### Aims

The overarching goal of our research is to build on existing services and initiatives, to develop acceptable and sustainable psychosis detection systems and management pathways, and to improve outcomes for people with psychosis in Malawi. Our specific aims are:

1. To understand how perceptions and thoughts that would be recognised in diagnostic manuals as ‘psychosis’ are experienced and conceived of among people with lived experience (PWLE), caregivers, and HSAs in Malawi, and how these influence help-seeking and preferences for care;

2. To develop and validate a screening tool as part of a psychosis detection system in Malawi that is accurate, useful, and acceptable to PWLE, HSAs, and caregivers, and which facilitates engagement and reduces DUP;

3. To formalise a readily implementable psychosis management plan, emphasising community-level psychosocial interventions, with facility-based physical health care and receipt of antipsychotic medication, that is acceptable to PWLE, caregivers, HSAs and health workers;

4. To evaluate the implementation processes, effectiveness and cost-effectiveness of the psychosis detection and management system in improving outcomes prioritised by PWLE, caregivers, and health workers.

## Materials & methods

We will integrate the programme design and evaluation tool, Theory of Change (ToC), into the UK Medical Research Council (MRC) Guidance for Developing and Evaluating Complex Interventions [17, 18] to enhance multiple stakeholder engagement and embed our interventions in the local context [19], and to address implementation processes and outcomes throughout [20]. The PRIME project developing integrated district mental healthcare plans in Ethiopia, India, Nepal, South Africa and Uganda [21] used this approach and found it was helpful in (a) supporting systematic thinking around complex interventions, (b) making assumptions explicit early in the process, and (c) developing consensus around outcomes. Another advantage of this approach is the commitment of ToC to an ongoing process of reflection. This allows adaptation as barriers to implementation arise, and new evidence comes to light, requiring pathways to be changed and strengthened. This is also harmonious with the Quality Improvement activities that are valued in Malawi’s Government initiatives.

Our framework for PROMISE has four work packages (WPs): intervention development (WP1), feasibility testing (WP2), piloting (WP3), and implementation with evaluation (WP4) in an iterative process. Developing a context specific ToC within the first three WPs to underpin the psychosis detection and management system with stakeholders will ensure we have an explicit impact pathway, facilitate the translation of research into practice tools and allow a theory driven investigation of the mechanism(s) of action. Overall, this will ensure we have an intervention fit for context as developing contextually relevant interventions is a key emerging concern within global mental health.

A key aspect of our process is to work closely with PWLE and other stakeholders, collaboratively identifying what positive outcomes and what real world impact they want to achieve, to determine pathways through which change can be effected using available resources. WP1 will thus develop locally embedded plans and success indicators that are acceptable and feasible within resource constraints. This will allow us to incorporate evidence from other settings if relevant and helpful, and adapt existing evidence-based interventions as appropriate.

Our approach will support a flexible but robust approach to find effective ways of identifying and managing psychosis, without imposing methods that may not be relevant, practicable, or desirable to PWLE, caregivers, and health professionals in Malawi. This shared vision as to what is desired and how coordinated actions will bring that about will foster the motivation across stakeholders to sustain the intervention following the research.

### WP1—Development of a psychosis detection and management system

In WP1, we seek to better understand: how ‘psychosis’ is conceived and experienced; what idioms of distress and traditions of knowledge are used to articulate experience; how conceptions, experiences and environments influence help-seeking and management, priorities, and preferences for care; and, what outcomes are desirable among PWLE and their families. We also seek to enhance our understanding of these issues in relation to traditional and religious healers, as well as health-workers including HSAs, Primary Care Health Centre and District Mental Health Team staff. We will build on our existing collaborations and work conducted in Healthy Lives, Generation Malawi [22, 23] to do so.

#### Activities

The activities for WP1 will include exploring and seeking to understand how PWLE can be supported to contribute to our research: both as qualitative participants in WP1 itself and–through ongoing engagement with the research team–as stakeholders in the intervention and shapers of this. Methods associated with Participatory Action Research, such as Photovoice, will be used to go beyond a sole focus on discourse into the realm of perception and experience through photography. Photovoice will: enable people to record and reflect on their perceptions, experiences, and concerns; promote knowledge and facilitate open communication about psychosis and its impact on individuals and families through group discussion of images; and, reach and inform health policy makers to help bring about change [24]. WP1 will produce research findings that will result in the development of a prototype detection and management intervention within 18 months.

To enhance what is already known about experience of psychosis within Malawi and elsewhere in Africa, a narrative, scoping review will be carried out on qualitative studies of madness/psychosis in Africa to date. Thereafter, WP1 activities will occur in two districts: one in Central (Salima) and one in Southern (Chiradzulu) Malawi. Within each district, key informants will be drawn from both an urban/peri-urban area and a rural setting.

The key informants are PWLE and their families, other formal and informal caregivers, traditional and religious healers, and healthcare staff (in particular, HSAs)—see Table 1. A total of 12 PWLE and 12 carers will be purposively sampled, with the assistance of Peer Support Workers (PSWs) from the Mental Health Users and Carers Association (MeHUCA) of Malawi and the Chiradzulu District Hospital (CDH) mental health clinicians. The latter will identify those with psychosis in community settings, including some with experience of secondary and tertiary care and prison, who will be invited to participate.

**Table 1 pone.0293370.t001:** WP1 activities to co-produce a psychosis management and detection system.

**Research questions**	**Methods**	**Key informants/participants**	
		**Community**	**Healthcare**
*What does the scientific literature say about the perception of psychosis in LMICs*?	Systematic reviews	**-**	
*What is the lived experience of people living with psychosis*?	In-depth interviews and focus groups (n = 24); Participatory empowerment using Photovoice (n = 12)	PWLE Family/caregivers	**-**
*What are the needs*, *perceptions of mental health and views of involvement in identification and referral among HSAs*?	Survey methods (n = 40)	-	HSAs
	In-depth interviews and focus groups (n = 20)	-	HSAs
*What are stakeholders’ views on psychosis detection and management systems*?	Key Informant Interview and Focus groups (n = 28)	PWLE Family/caregivers Traditional Healers Religious Healers	HSAs PHC staff DMHT staff
*What is a contextually appropriate and feasible programme theory for a psychosis detection and management system in the two districts in Malawi*?	Theory of Change workshops 1&2 (n = 20 per district)	PWLE Family/caregivers Traditional Healers Religious Healers	HSAs PCHC staff DMHT staff Government representatives

Key: PCHC = Primary Care Health Centre; DMHT = District Mental Health Team

Photovoice data collection will include four stages. The first will involve consent and training. The second stage consists of individual meetings where participants verbally reflect on each photograph using the SHOWED technique, previously used in Photovoice research [25]. The third stage is a group discussion where participants present selected pictures using the SHOWED technique. The other participants engage in dialogue to share similar or differing stories of experiences during the photograph presentations and ask each other questions. The final stage is a stakeholder meeting where health providers will be invited to hear the presentations. The stakeholders will be encouraged to ask follow-up questions to shed light on implementation strategies.

We will also conduct qualitative and quantitative research with the available sample of 40 HSAs, including self-completed questionnaires: the Community Attitudes toward Mental Illness scale, the WHO mhGAP pre- and post-knowledge test, and a confidence in identifying mental disorders questionnaire which have been used before in Malawi [14, 26]. Both data types will support a longitudinal understanding of HSA perceptions of mental health, experiences, and needs as health-workers, and perceived obstacles and enablers to supporting PWLE of psychosis and their caregivers. In each district, a social science team will conduct focus groups and in-depth interviews with a smaller sub-sample of 10 HSAs. Respondents will be purposively sampled, taking account of seniority, gender, and age. These focus groups, interviews, and surveys will be repeated each year of the project to understand ongoing experiences of HSAs, changes in their perspectives, and views on the intervention.

Additional qualitative data will be gathered from up to 28 key informants from the community and the health care system to understand diverse views on psychosis detection and management systems. This will be completed through key informant in-depth interviews and focus groups with: PWLE; family, and other caregivers; traditional and religious healers; and, HSAs and healthcare staff.

All the qualitative data will be audio-recorded, transcribed, and translated from Chichewa (the main language used in Malawi) to English. We will employ a thematic content analysis. The data analysis will involve several stages, including submersions, coding, and categorising to develop themes, helping inform the ToC development.

The findings from the mixed-methods approach will raise awareness and motivate change through the development of a psychosis detection and management system. Co-production with stakeholders will include collaboratively identifying what real-world impact they want, charting causal pathways through which change can be achieved in their context using available resources, and potential areas for psychosocial intervention consistent with cultural norms. The resulting ToC Roadmap will identify actionable findings relative to implementation strategies and stakeholder data to understand feasibility. This will inform the draft of a psychosis detection and management manual in Chichewa, enhanced by the findings of the literature reviews and recovery narratives from PWLE. We anticipate that those recovery narratives will also be able to be used, subject to informed consent, as a form of social contact with PWLE to reduce stigma.

### WP2—Feasibility testing of the psychosis detection and management system

A diagnosis of psychosis can help explain unusual experiences and behaviour to those affected and others, increase tolerance, reduce distress and stressful social obligations, and have functional value towards recovery [27]. This may be especially so if moral or supernatural causal attributions are prevalent, as in Malawi. However, a diagnosis may also be perceived as a limiting label, devalue pre-existing understandings of the experience, and increase stigmatisation for the individual and the family. More generally, psychiatric diagnosis can act as a vehicle for conceptions of self and society that emphasise cultural norms within HICs, and require careful consideration when used in the majority world [28, 29]—not least given concerns about biomedicalisation in global mental health [30]. Work conducted in some LMICs about the impact of a diagnosis of psychosis suggests that paced, individualised, and collaborative approaches are most valued [31]. These issues will be discussed with HSAs as part of their training. Our approach will be to encourage HSAs to take time and seek additional information if required to detect possible/probable cases.

*Activities*. WP1 will generate a ToC Roadmap and a draft of a psychosis detection and management manual. WP2 activities, therefore, focus on: a) translating these into a finalised manual; b) development of feasibility measurement methods; c) understanding HSA views of these; d) supporting HSAs to use the materials and procedures with a group of adults; and e) reviewing the final prototype manual and procedures.

WP 2 feasibility testing will be done in the sites where WP 1 was completed. This will allow feasibility testing in locations where community support has already been established. Given that the draft manual will have implications for both the community and the healthcare system, the key informants in this WP are PWLE and their caregivers, traditional and religious healers, HSAs, and other healthcare staff (see Table 2 below).

**Table 2 pone.0293370.t002:** Feasibility testing of the psychosis detection and management system in WP2.

**Research questions**	**Methods**	**Key informants/participants**	
		**Community**	**Healthcare**
*How can the feasibility of the psychosis detection and management system be measured in context*?	ToC workshop 4 (n = 10 [EB1] per district)	-	HSAs PHC staff DMHT staff Government representatives
*What is the feasibility of the psychosis management and detection system in Salima and Chiradzulu*?	ToC workshops 3 and 5 (n = 20 per district)	PWLE Family/caregivers Traditional Healers Religious Healers	HSAs PHC staff DMHT staff Government representatives
	Survey methods (n = 40)		HSAs
	Feasibility testing	People with possible psychosis (n = 20)	HSAs (n = 10)

Key: PCHC = Primary Care Health Centre; DMHT = District Mental Health Team

The first WP2 ToC workshop (ToC 3 overall) will review our understanding of the ToC Roadmap, review the draft manual, and consider the implementation strategies that will be needed to successfully deploy the intervention.

The second WP2 ToC workshop (ToC 4 overall) will include healthcare colleagues only, considering the healthcare elements of the intervention, to review the implications of the draft manual for the delivery of current services, and to develop feasibility and fidelity-to-manual measures. The third and final ToC of WP2 workshop (ToC 5 overall) will consider the final prototype manual and procedures alongside the feasibility testing data.

Given the HSAs are the group of professionals we are focussed on in this programme, their views of the draft manual and procedures will be critical. We will qualitatively and quantitatively re-survey 40 HSA’s (from those surveyed in WP 1). This is also two-thirds of the cohort of HSA’s who will be involved in the roll-out of the approach in WP3. This continuity reinforces the innovation pathway, by strengthening engagement with this group of professionals through early sight of draft materials and facilitating co-production via shared perspectives—thus shaping the final prototype manual and materials.

We will train 10 HSA’s in one of the two districts in WP1, in both the urban and rural setting, to use the draft manual and procedures to set up the first deployment of the approach. This will also require the training of Primary Care Health Centre and District Mental Health Team staff in the psychosis detection and management system, and in particular to support and supervise HSAs. This approach will then be ‘beta-tested’ within the regular working day of HSAs for two months to test it in practice. Any challenges will be logged in a risk register and solutions found with the Community Advisory Board. We plan to conduct feasibility testing on 20 people with possible psychosis, referred to them through the community or from healthcare staff.

### WP3—Piloting of the psychosis detection and management system

There is clinical trial evidence to support the efficacy of illness education and support, family interventions and antipsychotic medication, in acute and established psychosis, in Ethiopia, India and other LMICs [32–34]. There is also evidence that informal healthcare providers in some LMICs can be supported to collaborate with facility-based healthcare workers [35], and that this can be cost-effective [36]. In Malawi, we will build upon three recent initiatives. Wright & Chiwandira [37] have shown that it is possible to build capacity for community mental health care, including psychosis, with a district-wide task-sharing intervention with HSAs. [name] et al. [14] demonstrated that materials from the WHO mhGAP—a popular if not uncontroversial tool for guiding mental health care in low resource settings [38]—can increase primary healthcare workers’ knowledge and confidence in providing care for people with mental health conditions in Mulanje, southern Malawi. The Malawi Quick Guide to Mental Health (www.smmhep.org.uk) was published in 2020 to provide practical information for all healthcare workers in the assessment and management of mental disorders.

#### Activities

The key activities in WP3 will be to pilot the prototype manual and procedures of the psychosis detection and management system to N = 268 people to identify an anticipated N = 150 who screen positive for psychosis. This will be carried out sequentially, district by district, in the two districts involved in WPs 1 and 2 (Salima and Chiradzulu) and a third district (Ntcheu), which is equidistant between the others. The key informants in this WP are PWLE and their families, formal and informal caregivers, traditional and religious healers, HSAs, and clinic staff in Primary Health Centre and District Mental Health Teams. A process of engagement needs to be developed in the new Ntcheu district involved in WP3. This will be completed through ToC 6 workshop with PWLE and their families, and the other stakeholders above. Table 3 below gives an overview of WP3 activities.

**Table 3 pone.0293370.t003:** WP3 piloting of the psychosis detection and management system in 3 districts.

**Research questions**	**Methods**	**Key informants/participants**	
		**Community**	**Healthcare**
*What are the contextual adaptations required to implement the psychosis detection and management system in Ntcheu*?	ToC workshop 6 (n = 20 in Ntcheu)	People with lived experience Family/caregivers Traditional Healers Religious Healers	HSAs PHC staff DMHT staff Government Rep
*To what extent can HSAs trained in the psychosis and management tool accurately detect and refer people with psychosis to further care*?	Validation study (n = 268 screened)	People with possible psychosis	**-**
*Can the psychosis detection and management tool be delivered with fidelity by HSAs*?	Fidelity assessment (n = 60)	-	HSAs
*How did people with psychosis experience the detection and management process and what are the views of their diagnosis*	Qualitative interviews (n = 20 across three districts)	People with psychosis	-
*How did HSAs experience the detection and management process*? *How have their views on people with psychosis have changed*?	Qualitative interviews (n = 20 across Salima and Ntcheu)	-	HSAs
*What is the impact of the psychosis management and detection tool on service utilisation*?	Review of district health data	-	-

We will train 20 HSAs in three districts (n = 60) in the prototype psychosis detection and management system, to (a) screen for psychosis and engage with a management system, (b) provide community-based brief psychosocial interventions, and (c) use referral routes to consultations with a mental health specialist when the presentation is complex. This will situate the HSAs explicitly within a healthcare pathway and equip them with the knowledge and skills to support earlier detection and delivery of elements of care at the village level. We will train Research Assistants (RAs) to administer the Present State Examination gold-standard diagnostic interview as part of the WHO’s SCAN (WHO, 1997). This will be used to screen positive and negative cases (validation study). The RA will facilitate community-based psychosocial interventions for people who screen positive for psychosis. Inter-rate reliability of diagnosis and outcome measures at baseline will be established.

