## Introduction

Psychoses–principally schizophrenia and related conditions, including affective psychosis–can be experienced as deeply distressing and disabling conditions. Around 50% of people with psychosis in High Income Countries (HICs) will have ongoing symptoms and social and occupational functioning difficulties (APA, 2013). In one particularly comprehensive study, conducted in Finland, the combined lifetime risk of all psychoses was around 3%, with a prevalence of 1% [1]. The global point prevalence of schizophrenia is estimated to be 0.3–0.6% [2, 3].

Duration of untreated psychosis (DUP) is a key issue of clinical and public health concern. A longer DUP of even a few weeks or months has been consistently linked to worse outcomes in terms of more severe symptoms, worse social, vocational, and overall functioning, and reduced quality of life. This has been reported in many countries around the world, including low- and middle-income countries (LMICs) within Africa [4, 5]. The most cost-effective interventions for schizophrenia in Nigeria include community-based treatment with older antipsychotic drugs plus psychosocial support or case management [6]. Clinical trials indicate that antipsychotic drug treatment leads to quicker symptom relief, reduces the risk of relapse, and probably improves quality of life [7], and that psychosocial interventions such as illness education and support reduce relapse risk [8]. Notably, however, antipsychotic drugs can have unpleasant adverse effects which reduce their acceptability [9].

Malawi is a sub-Saharan African country with approximately 15 million people under the age of 30. No studies of the prevalence of psychosis generally or schizophrenia in Malawi have been conducted, but the increased risk of schizophrenia among the young and those living in poverty [10] are reasons to think it may be higher than in HICs. The prevalence of HIV/AIDS, malaria, and cannabis use [11, 12] could mean that organic and substance-induced psychoses are particularly common. Epidemiological surveys also suggest that brief psychoses could be more common in LMICs such as Nigeria than HICs [13].

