#### Validation study

A power calculation, using Python, identified that we will need to screen 268 people with ‘possible’ psychosis to identify 162 ‘true positives’ to have at least 80% power (alpha 0.05) to detect a change percent value of specificity of the diagnostic tool from 80% to 90%. Initial case-finding of people with ‘possible’ psychosis will result from awareness-raising in the community and from training HSAs. People with possible psychosis will then be assessed by HSAs using the screening tool. All people who are considered to have psychosis based on the screening assessment (‘probable’ psychosis) and a random sample of screen negatives will undergo the gold standard diagnostic assessment administered by the RAs. The RAs will be masked to the outcome of the screening test. The gold standard diagnosis will include any diagnosis within the ‘schizophrenia or other primary psychotic disorders’ section of ICD-11, and affective psychosis, but will exclude organic or substance-induced psychoses. We will investigate sensitivity, specificity, positive and negative predictive values. The key concerns are to minimise false positives of a definitive psychosis diagnosis and to detect those with ongoing (not brief) psychosis that would benefit from an intervention that can be provided. We will use multivariate analyses to investigate possible predictors of inaccurate diagnosis (e.g. gender, educational level, age) to inform further implementation.

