#### Evaluating impact on service utilisation

We will conduct an interrupted time series study to evaluate the impact of the detection component (case-finding, diagnosis, referral, and engagement) of the psychosis detection and management system on service utilisation. Following the HSA screening assessment, people with probable psychosis will be referred to the appropriate facility in the care pathway, depending on severity. We will establish a simple, paper-based, case registration system in all the potential referral facilities, including private sector facilities, at least three months prior to initiating case-finding in that district. This will create sufficient baseline data time points in the pre-intervention period to allow us to assess levels of service utilisation for people with psychosis (new and existing) prior to the intervention and during the implementation of the detection system. This method has been used previously in Malawi to investigate the impact of an intervention on general mental health contacts with facilities [14]. We will use segmented linear regression using aggregated monthly utilisation data to assess whether the detection system leads to a significant increase in utilisation of each type of service beyond pre-intervention trends [39].

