#### Activities

*Intervention cohort study without controls / pre-post sequential group design*. The analysis of individual outcomes will use appropriate descriptive statistics to present the outcome in each district as well as the overall statistic for all three districts. The outcome data will be stratified by health equity indicators (sex, age category, urban/rural residence) and by drop outs and loss to follow up. A sample size of 150 will be sufficient to detect a pre-post improvement of 20% overall (across the four sub-scales) of the WHOQoL primary outcome measure with a power of 90% (alpha = 0.05). The data will have a three-level structure with repeated outcomes measures collected with individuals clustered within three separate assessment centres. It is reasonable to assume that different data from people with psychosis in the same centres will be correlated and measurements on the same person even more highly correlated. To handle this data structure we will use Mixed Models (including fixed effects and random latent effects) using the appropriate model for the distribution of outcome. For the continuous scaled primary outcome WHOQoL, a linear mixed effect model will model change before and after intervention to estimate mean difference as well as the moderating effects of key health inequity measures (gender, urban/rural residence, socio-economic status) and process indicators (e.g. engagement with facility-based and community-based interventions).

The final selection of outcome measures for the evaluation will be informed by PWLE of psychosis and other stakeholders, and Theory of Change roadmaps (ToC 1; ToC 2; ToC 3; ToC5) inclusive of agreed indicators of success. Quality of life is a valued outcome for both psychosocial interventions and antipsychotic medication, and is therefore the current proposed primary outcome measure. The range of potential measures are indicated in Table 5 below with outcome measures carried out at baseline (WP3) and at 6 and 12 months (WP 4). This allows for the incorporation of other measures prioritised by PWLE and other stakeholders, such as food insecurity [42], and will give enough time for participants to engage with the innovation to investigate feasibility, fidelity, cost-effectiveness and outcomes.

**Table 5 pone.0293370.t005:** WP4 anticipated outcome measures.

**Focus**	**Measure used to capture focus**	**Baseline (WP3)**	**6 months (WP4)**	**12 months (WP4)**
Primary outcome PWLE				

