There is also a risk that people who screen positive for ‘possible psychosis’ and interview as ‘probable psychosis’ regard themselves as definitely diagnosed before a formal diagnostic interview has been done by the RAs. We will minimise this risk by clear written communication with terminology and content agreed with our Lived Experience Advisory Panels (LEAPs). There is also a concern that some people in those groups could benefit from intervention that is not available to them. Our LEAPs will input into development and implementation of the interventions in each district, and knowledge of what support is available in the community. Tailored information for possible / probable / confirmed psychosis will be available at a minimum.

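### The article is inconsistent on whether the WP4 cohort is everyone who screens positive or only those with a confirmed psychosis diagnosis, and the primary WHOQoL estimate depends on which

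*Protocol article*

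**What the plan says.** Several statements point to entry on the screening result:

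- WP3, Activities: 268 people are to be piloted "to identify an anticipated N = 150 who screen positive for psychosis".
- WP3, Activities: "The RA will facilitate community-based psychosocial interventions for people who screen positive for psychosis".
- Evaluating impact on service utilisation: after the Health Surveillance Assistant's screen, "people with probable psychosis will be referred to the appropriate facility in the care pathway".
- WP4, Activities: the cohort is sized at 150, and Table 5 takes its baseline in WP3.

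Other statements point to a confirmed diagnosis, or do not fit the first group:

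- WP4, Activities describes the participants by the condition: "It is reasonable to assume that different data from people with psychosis in the same centres will be correlated".
- Ethical considerations, speaking of people whose psychosis is so far only possible or probable: "There is also a concern that some people in those groups could benefit from intervention that is not available to them".
- Validation study: the 268 screened are expected to yield 162 true positives.

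The Validation study section also says who has the gold-standard interview: "All people who are considered to have psychosis based on the screening assessment (‘probable’ psychosis) and a random sample of screen negatives". That reference diagnosis covers primary and affective psychoses "but will exclude organic or substance-induced psychoses". The Introduction warns that local conditions "could mean that organic and substance-induced psychoses are particularly common". The WP4 text stratifies outcomes by sex, age, residence and dropout. It does not mention the reference diagnosis.

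**The concern.** WP4 has no control group, so the mean pre-post change in WHOQoL is the effect estimate. It also feeds the cost-effectiveness ratio, which assumes that baseline scores and costs would otherwise have stayed as they were. Who is counted therefore matters more than it would in a controlled comparison.

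If everyone who screens positive is followed and analysed, the primary result includes false positives and people with organic or substance-induced psychosis, whom the article's own reference standard does not count as cases. Some may recover for reasons unrelated to the programme; others may have little to gain from it. If only confirmed cases are followed, 150 screen positives supply fewer than 150 people unless the screen makes no false-positive errors. The stated size and power then belong to a different group from the one analysed.

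**Working it through.** **Inputs from the article.** Validation study: 268 screened, 162 true positives, specificity 80% against 90%, power at least 80%, alpha 0.05. WP3 Activities: 150 screen positives. WP4 Activities: 150 participants, 20% improvement, 90% power, alpha 0.05. **Assumed:** sensitivity of 70–100%, because the article gives none.

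**1. The 268.** One-sample test of a proportion, two-sided:

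n = [(1.96 × √(0.8 × 0.2) + 0.842 × √(0.9 × 0.1)) / 0.1]² = 107.4 non-cases.

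With an assumed 40% of those screened being non-cases, 107.4 / 0.40 = 268.6, which reproduces the stated 268. The 162 (162/268 = 60%) is then most plausibly the number of gold-standard cases, leaving 268 − 162 = 106 non-cases. Read literally, as people positive on both screen and reference, 162 exceeds the 150 who are expected to screen positive at all.

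**2. The WP4 150.** This cannot be reproduced, because no baseline mean or standard deviation is given. It can be inverted to the standardised change it implies: d = (1.96 + 1.282) / √150 = 0.265.

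**3. Gold-standard negatives among screen positives.** True positives = 162 × sensitivity; false positives = 106 × (1 − specificity).

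| Sensitivity | Specificity | True positives | False positives | Screen positives | Share negative | Per 150 |
|---|---|---|---|---|---|---|
| 100% | 90% | 162.0 | 10.6 | 172.6 | 6.1% | 9 |
| 80% | 90% | 129.6 | 10.6 | 140.2 | 7.6% | 11 |
| 80% | 80% | 129.6 | 21.2 | 150.8 | 14.1% | 21 |
| 70% | 80% | 113.4 | 21.2 | 134.6 | 15.8% | 24 |

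Sensitivity and specificity both at 80% give almost exactly the planned 150 screen positives. That match does not show that these were the planning values.

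**4. Effect on the estimate if all are analysed.** With a share f of gold-standard negatives, the observed change is (1 − f) × change in cases + f × change in non-cases. The bias relative to cases is f × (change in non-cases − change in cases). For f of 6–16%, every 10-point difference between the groups moves the result by 0.6 to 1.6 points, up or down. If the non-cases do not change at all (an assumption) and f = 14%, a 20% gain becomes 20 × 0.86 = 17.2%. Power, with the same standard deviation of change, is Φ(0.265 × 0.86 × √150 − 1.96) = 80%.

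**5. Effect on power if only confirmed cases are analysed.** At f = 14%, 150 × 0.86 = 129 people, and power is Φ(0.265 × √129 − 1.96) = 85% instead of 90%.

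**The case against.** The strongest reply is that screen-based entry is an inference. No sentence states the WP4 entry rule, and the link rests on a matching 150 and a baseline taken in WP3. That is correct. A reader might infer that the article admits people to WP4 on the screen alone, but the documents do not establish it.

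The sentence on the research assistants can also be read another way. It follows a description of their diagnostic interview, and they are masked to the screening result, so a positive result there could mean positive on their own interview. This reading is open. It does not cover the 150, which the article describes as screen positives, or the referral rule, which follows the Health Surveillance Assistant's screen.

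The remark in Ethical considerations may refer only to scarce local services, or to possible cases who never screen positive. It is suggestive, not decisive.

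An analysis set is normally defined in a full protocol or analysis plan that is not shown here, so its absence alone would be no finding. What remains are statements within the article, about who is treated, referred and counted, that do not agree.

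It is also fair that an as-delivered cohort is a legitimate population for evaluating a detection and management system. That is a reason to keep it as a named analysis. It does not settle which population the primary result describes.

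**Conclusion.** The concern holds as an inconsistency with a measurable consequence. Entry to WP4 appears to follow the screening result, while other statements point to confirmed psychosis, and the 150 and 162 cannot both stand as worded. If all screen positives are analysed, about 6–16% of the cohort (9 to 24 of 150) would be gold-standard negative. This rests on 162 cases and 106 non-cases, the article's specificity range and an assumed sensitivity of 70–100%.

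Three stronger readings go too far:

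- **That the contamination inflates the result.** The direction is unknown, because it depends on how non-cases change, and the article gives no information on this.
- **That the share is higher because organic and substance-induced psychoses are common.** The Introduction says they could be but gives no figure, so nothing beyond the range above can be sized.
- **That a confirmed cohort of 150 is out of reach.** With 162 cases, 150 confirmed would need a sensitivity of 150/162 = 93%. The screen positives would then number 160.6 to 171.2 (150 plus 10.6 to 21.2), not 150.

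Nor does contamination of this size make the result uninterpretable. It leaves unclear which population the result describes.

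**What to change.** 1. In WP4, Activities, state the entry rule for the cohort.
2. Define the primary analysis set as screen positives whose WP3 gold-standard diagnosis is positive. Report not-confirmed cases and organic or substance-induced cases as separate descriptive groups.
3. Keep all screen positives as a secondary, programme-as-delivered analysis, and use it for the cost work as well.
4. Reconcile the 150 in WP3 and WP4 with the 162 in the Validation study, saying whether 162 counts gold-standard cases or people positive on both screen and reference.
5. Restate the WP4 size or power for the confirmed set, with the sensitivity and specificity assumed.
6. Reconcile WP3, Activities with Ethical considerations on who is offered the intervention at each diagnostic stage. Which rule applies is for the investigators to state.

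No new data are needed, since every screen positive already has the reference interview. The cost is a primary set about 6–16% smaller than 150 and somewhat lower stated power (about 85% in the worked case). Keeping 150 confirmed cases at 80% sensitivity and specificity would instead need 150/0.86, about 175 screen positives. At the same yield that means screening about 268 × 175/150.8 = 311 people.
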